**Table 1 Tab1:** **Schedule of assessments in**
***Recovery***
**MANTRA**

**Assessment**	**Eligibility screening**	**Baseline**	**Daily, for 6 weeks**	**Weekly, for 6 weeks**	**End of 6 weeks**	**6-month follow-up**
Participant’s information, informed consent, screening	X					
Clinical and demographic information		X				
Body mass index		X		X	X	X
Eating Disorder Examination Questionnaire		X			X	X
Depression Anxiety Stress Scale		X			X	X
Work and Social Adjustment Scale		X			X	X
The Autonomous and Controlled Motivations for Treatment Questionnaire		X			X	
Eating Disorder Examination Questionnaire - Short				X		
Daily assessments			X			
Client Service Receipt Inventory						X
Visual analogue scale: confidence and motivation to change		X			X	
Cognitive flexibility		X			X	
Patient alliance with therapist		X			X	
Patient alliance with peer mentor				X		

Daily assessments employ visual analogue scales and follow the day reconstruction method to measure daily mood, motivation, confidence, treatment adherence and connectedness.

### Randomization

Participants will be randomized by an independent researcher using stratified randomization by centre and illness severity (severe illness will be defined as BMI <16 kg/m^2^). Once the database has returned a participant’s group allocation, no changes can be made.

### Participants

Patients aged 16 or over who are referred to one of the participating specialist adult outpatient eating disorder clinics with a primary DSM-5 diagnosis of anorexia nervosa or other specified feeding or eating disorder with a BMI of 18.5 kg/m^2^ or below are offered an opportunity to participate in the research. ‘Other specified feeding or eating disorder’ will be defined as having features of anorexia nervosa but missing at least two of the four diagnostic criteria. Patients with insufficient knowledge of English, or with severe mental or physical illness needing treatment in its own right (for example, psychosis or diabetes mellitus) will be excluded. The participants will be reimbursed for their time at the completion of all assessments.

### Sample size

Previous research suggests that the effect size for increases in BMI subsequent to a guided self-help intervention is 0.29 [6]. To detect the same level of change in our primary outcome variable (BMI) using a paired-samples *t* test (*α* = 0.05, *β* = 0.20), a minimum of 90 participants would be required per study arm. However, owing to limited resources and because this is a feasibility study, we expect to recruit 75 participants per arm (resulting in total *N* = 150). This would enable us to detect an effect size of 0.33 or larger (*α* = 0.05, *β* = 0.20).

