In total, 10 to 15 peer mentors will be trained, to allow for attrition. The purpose of the guidance is not to provide an additional stand-alone intervention, but rather, to offer support to patients in using the self-help materials effectively and purposefully. Peer mentors are individuals with past experience of eating disorders who have sufficient time for training, supervision and coaching and are trained in professions allied to medicine or equivalent (psychology, counselling) or teaching. Individuals with clinically significant levels of baseline anxiety, depression or eating disorder symptoms are excluded. Comprehensive training for task-sharing interventions involves three important components: participation in an introductory workshop delivered by an expert, reading or review of workbooks or other written materials that detail the intervention, and administration of the intervention under close supervision of treatment experts [2]. Peer mentors will receive all of these training components prior to delivering the *Recovery* MANTRA intervention.

The curriculum currently used for training and supervision of carer coaches will be adapted for training peer mentors. In particular, the peer mentors will receive three days of training in motivational interviewing, during which they will also become familiarized with the *Recovery* MANTRA materials and practise using the online text-chat delivery system. For the duration of their involvement in the project, the peer mentors will also receive weekly clinical supervision and will undergo regular assessment of their eating disorder symptoms and mood. Copies of the text-chat messages between the peer mentor and the participant will be used for supervision and to assess treatment quality and fidelity.

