### Outcome assessment

The primary outcome variable is patient BMI at the end of the 6-week intervention (treatment as usual versus *Recovery* MANTRA). The secondary outcome variables are patient BMI at 6-month and follow-up and eating disorder symptoms (assessed by EDE-Q scores) at 6-week and 6-month follow-up (treatment as usual versus *Recovery* MANTRA). The hypothesized mediators and moderators of primary and secondary outcomes include mood (DASS-21), perceived work or social adjustment (Work and Social Adjustment Scale), motivation and confidence to change (visual analogue scale and ACMTQ), cognitive flexibility, and perceived alliance with therapist and peer mentor. Moreover, the trajectories of change in eating disorder symptoms (weekly EDE-QS), perceived alliance with peer mentors (assessed weekly), and mood, confidence or motivation, connection to others, hope and adherence or satisfaction with treatment plan (assessed daily via ultra-brief surveys) will predict the primary and secondary outcomes. Exploratory outcomes include the impact of guidance delivery on peer mentors’ eating disorder symptoms and mood (assessed via a feedback form) and treatment adherence or fidelity and acceptability (assessed via a feedback form) on secondary outcomes.

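### The stated detectable effect of 0.33 treats all 75 recruited per arm as analysed, so it holds only if week-6 BMI is essentially complete

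*Protocol article*

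**What the plan says.** The Sample size section (protocol article, Methods) takes an effect size of 0.29 from an earlier study, applies a paired-samples t test at alpha 0.05 and beta 0.20, and concludes that "a minimum of 90 participants would be required per study arm". It then accepts a smaller trial for reasons of resource: "we expect to recruit 75 participants per arm", 150 in total. The next sentence is "This would enable us to detect an effect size of 0.33 or larger", at the same alpha and beta. Nothing in the section separates participants recruited from participants with an outcome.

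Under Outcome assessment, "The primary outcome variable is patient BMI at the end of the 6-week intervention", compared between the two arms. Patient assessments has clinicians record weight at baseline and weekly for six weeks. Quantitative data analysis plans mixed-effects models on the repeated measures. The only mention of attrition is in the description of the guided self-help arm and concerns the mentors: "In total, 10 to 15 peer mentors will be trained, to allow for attrition".

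**The concern.** A detectable effect is a property of the participants who contribute an outcome, not of those who enter the trial. Here the two numbers are set equal without comment. The trial recruits from more than 25 outpatient services, and the article gives no reason to expect that every participant will have a BMI at six weeks.

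The figure matters because readers will judge a null result against it. The abstract says the results will determine whether a larger trial is worthwhile. The section already concedes 75 against the 90 it calculated as needed. Appreciable loss would widen that gap, and the reader would have no figure for it.

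**Working it through.** **Inputs.** From Sample size: 75 per arm, paired t test, alpha 0.05, power 0.80, stated effect 0.33. The article does not say whether the test is one- or two-sided; two-sided is assumed because it reproduces the stated figure. The article gives no participant loss rate, so 10%, 20% and 30% are assumptions chosen to show a range.

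**Formulas.** Power = P(|T| > t at 0.975), with T noncentral t.
- Paired test: df = n − 1, noncentrality d√n.
- Two independent arms of n each: df = 2n − 2, noncentrality d√(n/2).

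The detectable effect is the d that gives power 0.80.

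**Step 1: reproduce the plan's figure.** Paired, n = 75: d = 0.328, which rounds to the stated 0.33. The normal approximation agrees: (1.960 + 0.842)/√75 = 0.323. Power at d = 0.33 is 80.5%. Solving for d = 0.33 gives n = 74.02, or 75 when rounded up. The stated figure therefore uses all 75.

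**Step 2: how much slack there is.** Paired test:

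| Analysed per arm | Detectable effect | Power at 0.33 |
|---|---|---|
| 75 | 0.328 | 80.5% |
| 74 | 0.330 | 79.99% |
| 72 | 0.335 | 78.9% |
| 71 | 0.337 | 78.3% |
| 70 | 0.340 | 77.7% |

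At 72 the unrounded value is 0.3347, so to two decimals 0.33 survives the loss of three per arm (3/75 = 4%). Power falls more than two points below 80% only from about five lost per arm (5/75 = 6.7%).

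**Step 3: larger assumed losses.** Analysed numbers are 75 × 0.9 = 67.5, taken as 68; 75 × 0.8 = 60; and 75 × 0.7 = 52.5, taken as 53.

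| Assumed loss | Analysed per arm | Paired detectable effect | Paired power at 0.33 | Two-sample detectable effect |
|---|---|---|---|---|
| 0% | 75 | 0.328 | 80.5% | 0.460 |
| 10% | 68 | 0.345 | 76.5% | 0.484 |
| 20% | 60 | 0.368 | 71.0% | 0.516 |
| 30% | 53 | 0.392 | 65.5% | 0.549 |

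With 67.5 and 52.5 unrounded, the paired power at 10% and 30% loss is 76.2% and 65.0%. The last column is an unadjusted comparison of the two arms, which is the form of the primary question.

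All these are complete-case figures. A participant with some weekly weights but no week-6 weight is counted as contributing nothing.

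**The case against.** The strongest reply is that nothing in the section is miscalculated. A reader might infer that the plan's own formula fails to give 0.33, or that any loss at all falsifies it. Neither is supported: the formula gives 0.328 at 75, and 0.33 to two decimals survives three losses per arm. That part of the reply stands. The defect is an unstated assumption of complete data, and its size depends on a loss rate that the article does not supply.

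Several further points have weight.
- The endpoint is only six weeks away, weights are taken by clinicians in patients already attending a service, and participants are reimbursed on completing all assessments. Loss may be small.
- The mixed model uses the earlier weekly weights, so the losses tabulated above are nearer to upper bounds than to expected values.
- The allowance for mentor attrition is workforce planning. It says nothing about how many participants will have a week-6 BMI, and no inference should be drawn from the contrast.
- Use of a paired test for a between-arm question is the larger problem. It moves the detectable effect from 0.33 to 0.46, whereas 10% loss moves it only to 0.345. Correcting the test while still entering 75 would, however, leave the present problem in place.

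It can also be argued that a condensed article leaves loss assumptions to a fuller document. That does not dispose of the point, because the article prints a specific figure and attaches it to the recruited number. One reservation remains: a one-sided paired test would need only 59 per arm for 0.33, leaving 1 − 59/75 = 21% spare. The article states neither a one-sided test nor any allowance, and the two-sided calculation with all 75 reproduces its figure directly.

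**Conclusion.** The point holds as a conditional one. The 0.33 at 80% power is correct for 75 analysed per arm and has no allowance for participant loss, so it describes the trial only if week-6 BMI is essentially complete. Below about 5% loss the difference is negligible. At 10% it is modest, and at 20% to 30% it is material, with about 71% to 65% power at 0.33 in place of 80%. These sizes rest on assumed loss rates, a two-sided test and complete-case analysis, and the mixed model would improve on them to an extent the article does not allow one to calculate.

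It does not follow that the trial is too small to run or should recruit more. The article describes an exploratory feasibility study and is open about falling short of 90 per arm. What needs correcting is the sensitivity figure given to readers.

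**What to change.** Keep 150 recruited and do not enrol more. In Sample size, state the number per arm expected to have a week-6 BMI, with the reason for that expectation. Replace the 0.33 sentence with the detectable effect for that number on the between-arm comparison, and say what standard deviation it is expressed in. A short range is enough: for an unadjusted two-sample t test, 0.46 with 75 per arm, and 0.48, 0.52 and 0.55 at 10%, 20% and 30% loss. Add that the planned mixed model on weekly weights may recover some precision.

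The cost is a sentence or two of text and a less favourable published figure. Recruitment, data collection and the planned analysis do not change.

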#### Primary

Is *Recovery MANTRA* associated with higher BMI at the end of the 6-week intervention relative to treatment as usual alone?

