## Methods

### Trial design

This is a multicentre, two-arm randomized controlled study (SHARED) exploring the efficacy of adding a guided self-help intervention (*Recovery* MANTRA) to treatment as usual for anorexia nervosa. The study received ethical approval from a National Research Ethics Service Committee (London Brent, approval number 14/LO/1347) and approvals from the research and development departments at South London and Maudsley NHS Foundation Trust, Barnet Enfield & Haringey NHS Mental Health Trust, Coventry and Warwickshire Partnership NHS Trust, Surrey and Borders Partnership NHS Foundation Trust, Worcestershire Health and Care NHS Trust, Cambridgeshire and Peterborough NHS Foundation Trust, Cumbria Partnership NHS Foundation Trust, Dorset HealthCare University NHS Foundation Trust, Leicestershire Partnership NHS Trust, Lincolnshire Partnership NHS Foundation Trust, South Essex Partnership University NHS Foundation Trust, Nottinghamshire Healthcare NHS Trust, Sussex Partnership NHS Foundation Trust and Kent and Medway NHS Trust. Recruitment will not begin at any individual centre until all approvals have been obtained.

After providing informed consent, participants are randomly assigned to either (1) *Recovery* MANTRA in addition to treatment as usual (*Recovery* MANTRA condition) or (2) treatment as usual alone (control condition). Participants are recruited from over 25 different specialist adult outpatient eating disorder services in the UK. Data are collected at baseline, during the intervention, after 6 weeks (that is, at the end of the intervention for those in the *Recovery* MANTRA condition), and at 6-month follow-up (Table 1). At the end of the study, individuals who had been randomized to the treatment as usual only control condition will be offered the *Recovery* MANTRA intervention materials (that is, vodcasts and workbook).

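### The sample size section applies a paired t test to a two-arm comparison, so its 0.33 is a within-arm figure; unadjusted, 75 per arm detects 0.46 between arms

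*Protocol article*

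**What the plan says.** The Sample size section starts from earlier research, reporting that "the effect size for increases in BMI subsequent to a guided self-help intervention is 0.29". It sizes the trial to detect that effect "using a paired-samples *t* test (*α* = 0.05, *β* = 0.20"), and concludes that "a minimum of 90 participants would be required per study arm". Citing limited resources and the feasibility nature of the study, it then settles on fewer: "we expect to recruit 75 participants per arm (resulting in total *N* = 150"). For that number it states: "This would enable us to detect an effect size of 0.33 or larger", again at α = 0.05 and β = 0.20.

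The comparison to be powered is set out elsewhere. Trial design says "This is a multicentre, two-arm randomized controlled study (SHARED"). The primary research question is whether the intervention is "associated with higher BMI at the end of the 6-week intervention relative to treatment as usual alone". Outcome assessment names the same contrast, and Quantitative data analysis examines group differences through a group-by-time interaction. Randomization is stratified by centre and illness severity; no matching of individuals across arms is described.

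**The concern.** A paired t test compares two measurements on the same people. Applied per arm, it asks whether BMI changes from before to after within that arm. It does not ask whether one arm ends higher than the other, which is the primary question. A between-arm contrast carries sampling error from both arms, so at the same n per arm and the same standardising SD its detectable effect is larger by a factor of about √2.

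The 0.33 is the only statement of sensitivity for the primary outcome in the article. A reader will take it as 80% power for a between-arm standardised difference of 0.33, and the calculation shown does not support that.

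**Working it through.** **Inputs.** From the Sample size section: α = 0.05, β = 0.20, effect 0.29, 90 per arm required, 75 per arm planned, 0.33 claimed. Sidedness is not stated; two-sided is assumed and one-sided is tried as a variant. Final figures use the noncentral t distribution. The normal approximation is shown so that each step can be checked by hand, with z(0.975) + z(0.80) = 1.960 + 0.842 = 2.802.

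**1. Reproduce the stated 0.33.** Paired test, n = 75 pairs:
- d = 2.802 / √75 = 0.323; noncentral t gives 0.328, which rounds to 0.33.
- Power of this test at d = 0.33 is 80.5%.
- The one-sided paired version gives 0.290, which does not match.

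So 0.33 is the two-sided, within-arm, pre-post figure for one arm of 75.

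**2. The same question between arms.** Independent two-sample t test, 75 per arm, no covariate:
- d = 2.802 × √(2/75) = 0.457; noncentral t gives 0.460.
- One-sided: 0.408. Neither version gives 0.33.

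The 0.46 also holds for a two-sample comparison of change scores if the effect is expressed in SDs of change, because the formula is then the same.

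**3. Power with 75 per arm (two-sided, unadjusted).** Power ≈ Φ(d × √(75/2) − 1.960):
- d = 0.33: Φ(2.021 − 1.960) = 52.4%; noncentral t 51.9%.
- d = 0.29: Φ(1.776 − 1.960) = 42.7%; noncentral t 42.3%.

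**4. Number per arm for 80% power.** n = 2 × (2.802/d)²:
- d = 0.29: 187; noncentral t 188.
- d = 0.33: 145; noncentral t 146.

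**5. Side check on the 90.** Paired test at d = 0.29: n = (2.802/0.29)² = 93.3, so 94; noncentral t gives 96. With 90 pairs, power at 0.29 is 77.7% and the detectable effect is 0.299, so 90 corresponds to about 0.30.

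**6. What baseline adjustment could do.** In raw BMI SD units the detectable difference is about 0.46 × √(1 − r²), where r is the baseline to week-6 BMI correlation. The article gives no r, so these values are assumptions:

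| r (assumed) | Detectable difference, raw BMI SDs |
|---|---|
| 0 | 0.46 |
| 0.5 | 0.40 |
| 0.7 | 0.33 |
| 0.9 | 0.20 |

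In SDs of change, the usual scale of a paired effect size, the adjusted figure is 0.46 × √((1 + r)/2). That is 0.42 at r = 0.7 and 0.45 at r = 0.9, so on that scale adjustment recovers little.

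**The case against.** The strongest reply is that the analysis will not be an unadjusted t test. Weights are taken at baseline and weekly, and the plan is a mixed-effects model with a group-by-time interaction. In raw BMI SD units, r of about 0.7 brings the detectable difference to 0.33, and a higher r brings it lower. This stands as a limit on the finding: 0.46 and 52% describe an unadjusted comparison, not the power of the design under every analysis. A reader might infer that the trial has only an even chance of detecting 0.33 whatever the analysis, and the article does not support that. The reply does not rescue the published statement, however. The section states no correlation, makes no adjustment argument and does not say in which SD the effect is expressed. It names a paired test, and that test alone yields its 0.33.

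It can also be said that 0.33 is arithmetically right for the test named. That is so; the fault lies in the choice of test.

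The feasibility label and limited resources explain recruiting 75 instead of 90. They do not turn a within-arm figure into a between-arm one.

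The 90 versus 96 discrepancy is small. An effect rounded down from just under 0.295 would need about 92 pairs, and 90 was not adopted. It is a note only.

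Three further inferences are tempting and are not made here:
- **No allowance for missing week-6 weights.** This is a condensed article, and silence on attrition is not a finding.
- **A null result would wrongly stop a larger trial.** The abstract says the results will inform that decision, but nothing in the article ties it to a significance test.
- **The 0.29 is definitely a pre-post effect.** The wording leans that way, but the article does not settle it.

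**Conclusion.** The point holds in a conditional form. The sample size statement uses a test that does not match the primary comparison, and its detectable effect of 0.33 at 80% power is a within-arm figure. For a two-sided 5% between-arm test without covariates, or on change scores in SD-of-change units, 75 per arm detects 0.46. Power is then about 52% at 0.33 and 42% at 0.29, against the stated 80% at 0.33. These figures assume two-sided testing, 75 analysed per arm and independent observations. A baseline-adjusted analysis may do better in raw BMI SD units, by an amount that depends on a correlation the article does not give. The planned N of 150 is not itself an error.

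**What to change.** Keep N = 150. In the Sample size section, remove the paired t test and the figure of 90 per arm, and replace the detectable-effect sentence with:

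> With 75 per arm, a two-sided 5% between-arm test has 80% power for a standardised difference of 0.46 (unadjusted).

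If the sponsor relies on a baseline-adjusted analysis, state instead the assumed baseline to week-6 BMI correlation r and the resulting figure, 0.46 × √(1 − r²), and say that it is in raw BMI SD units.

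This changes wording only, with no extra participants and no change to conduct. The downside is a less favourable stated figure, or an explicit correlation assumption that the sponsor must justify.

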### Recruitment

After initial assessment by the clinical team, patients will be informed about the study by the local principal investigator or clinical support officer at the study sites. All participants will be clearly informed of the voluntary nature of the study.

### Treatment arms

#### Treatment as usual

The group allocated to this condition will receive treatment as usual at the participating site and will also be asked to complete assessments on the Ieso Digital Health platform. Assessments and a minimal level of feedback will occur following the same schedule as for the *Recovery* MANTRA condition (see Table 1). Treatment as usual will vary between centres (for example group psychoeducation versus individual psychotherapy or versus nutritional support and medical monitoring). These differences will be assessed and taken into account when analyzing and interpreting findings.

#### Guided self-help (Recovery MANTRA)

Participants allocated to the *Recovery* MANTRA condition will receive self-help materials and weekly guidance from a peer mentor to supplement their treatment as usual. The self-help materials include a collection of short video clips (‘vodcasts’) that describe various strategies for behaviour change, anxiety management techniques, and recovery narratives generated by individuals with personal experience of eating disorders. The vodcasts are accompanied by (and signposted in) a self-care workbook. The workbook provides supplemental information and offers the rationale for the behaviour change steps proposed. The intervention materials were developed with the aim of increasing confidence to change, internalized motivation, connectedness to others and hope. In addition, the participants will be offered individualized support via online text chat (using a secure platform) through peer mentors for a maximum of one hour each week over 6 weeks. The peer mentor will contact the participants to introduce the materials and to provide information about the parameters of support (see Table 2 for programme of guidance).

